## Abstract

**Introduction:**

Rebound pain, transient and acute postoperative pain after the disappearance of regional block anesthesia, has been a concern in recent years. Insufficient preemptive analgesia and hyperalgesia induced by regional block are the main mechanisms. At present, the evidence for the treatment of rebound pain is limited. The esketamine, as an antagonist of the N-methyl-D-aspartate receptor, has been proven to prevent hyperalgesia. Therefore, this trial aims to evaluate the impact of esketamine on postoperative rebound pain in patients undergoing total knee arthroplasty.

**Methods/design:**

This study is a single-center, prospective, double-blind, randomized, placebo-controlled trial. Participants who plan to undergo total knee arthroplasty will be randomly assigned to the esketamine group (*N* = 178) and placebo group (*N* = 178) in a ratio of 1:1. This trial aims to evaluate the impact of esketamine on postoperative rebound pain in patients undergoing total knee arthroplasty. The primary outcome of this trial is the incidence of rebound pain within 12 h after the operation in the esketamine group and the placebo group. The secondary outcome will be to compare (1) the incidence of rebound pain 24 h after the operation; (2) the time to enter the pain cycle for the first time within 24 h after the procedure; (3) the first time of rebound pain occurred within 24 h after surgery; (4) the modified rebound pain score; (5) NRS score under rest and exercise at different time points; (6) the cumulative opioid consumption at different time points; (7) patient’s prognosis and knee joint function evaluation; (8) blood glucose and cortisol concentration; (9) patient’s satisfaction score; (10) adverse reactions and adverse events.

**Discussion:**

The effect of ketamine on preventing postoperative rebound pain is contradictory and uncertain. The affinity of esketamine to the N-methyl-D-aspartate receptor is about four times higher than levo-ketamine, the analgesic effect is 3 times higher than levo-ketamine, and there are fewer adverse mental reactions. To our knowledge, there is no randomized controlled trial to verify the impact of esketamine on postoperative rebound pain in patients undergoing total knee arthroplasty. Therefore, this trial is expected to fill an important gap in relevant fields and provide novel evidence for individualized pain management.

**Clinical Trial Registration:**

http://www.chictr.org.cn, identifier ChiCTR2300069044.

## Introduction

1.

The term ‘rebound pain’ was recently introduced to describe the temporary, acute postoperative pain that occurs after regional anesthesia sensory block has worn off, and which can be observed following peripheral nerve block and intraspinal anesthesia (1). To date, there is no clear definition of rebound pain. To better quantify rebound pain, Barry et al. (2) proposed a standardized reporting method: if the pain level transitions from well-controlled [numerical rating scale (NRS) ≤ 3] to severe (NRS ≥ 7) within 24 h after regional block, rebound pain is considered to have occurred. The mechanism of rebound pain is unclear, but may be explained by relatively sudden nociceptive pain from insufficient preemptive analgesia or regional block-induced hyperalgesia (1, 3). Other factors may include local anesthetic neurotoxicity, withdrawal reactions, potential pain-promoting effects, and individual or surgical factors (4).

Total knee arthroplasty (TKA) uses artificial materials to replace the knee joint to alleviate and eliminate inflammatory disease, pain, and tissue deformity. However, TKA also causes significant trauma and severe bone, soft tissue, and nerve damage. After TKA, 60% of patients experienced severe knee pain, and 30% experienced moderate pain (5). In China, the Consensus of Experts on Postoperative Pain Management for Adults has suggested that multimodal analgesia should be adopted for TKA. Multimodal analgesia includes non-drug and drug measures. The latter combines several drugs and drug delivery routes, including preventive analgesia, peripheral nerve block, patient-controlled analgesia, periarticular mixed drug injection analgesia, and oral/intravenous use of non-steroidal anti-inflammatory drugs and opioids.

In our medical center, single subarachnoid block anesthesia, instead of general anesthesia, has become the standard of care for TKA. It is relatively low-cost and simple to administer, has good analgesic effects, has a high safety rating, and has minimal cardiopulmonary effects. It is worth noting that subarachnoid block anesthesia, peripheral nerve block, and mixed drug injection around the joint are all regional block types, which can lead to transient, acute postoperative pain after wearing off (i.e., rebound pain). As an acute postoperative pain, rebound pain may cause adverse effects. It often occurs at night, eroding patient sleep quality and seriously affecting rehabilitation (6). Patients who are unaware of this adverse effect and experience unexpected pain may increase their use of oral medications, leading to further opioid consumption and increased emergency room visits (6). Rebound pain also reduces the benefits of a regional block, lowers patient satisfaction, and increases postoperative care costs (6).

Evidence on rebound pain treatment is limited. In patients undergoing arthroscopic rotator cuff repair, dexamethasone added around the nerve with ropivacaine to block the scalene muscle space can reduce pain aggravation after subsidence of the regional block and reduce rebound pain incidence in the first postoperative week (7). Dexamethasone may make the nerve block fade more smoothly, extend its duration, and have anti-inflammatory effects. However, using dexamethasone as an auxiliary anesthetic for a peripheral nerve block is an over-indication, the long-term safety of which has not been evaluated. High-dose peripheral dexamethasone may also lead to a risk of wound infection and neurotoxicity (8). Perineural application of dexmedetomidine in arthroscopic rotator cuff repair can reduce postoperative pain scores and delay rebound pain during the first 48 post-surgical hours (9, 10). Combining two or more nerve blocks and prolonging the block duration significantly reduces rebound pain and oral opioid use (11–13). However, combined use of nerve blocks may increase the risk of local anesthetic poisoning and nerve injury. Thus, continuous peripheral nerve block is more suitable for inpatients and challenging for use in those who are discharged, for whom it means considerable workload and increased economic burden (8).

N-methyl-D-aspartate (NMDA), an excitatory glutamate receptor in the neuronal membrane, plays a crucial role in developing anti-central sensitization. Ketamine is a non-competitive NMDA antagonist with a 2–4-h half-life. It acts on brain and spinal cord neurons and has been used to reduce opioid-induced hyperalgesia. The affinity of esketamine to NMDA receptors is about four times higher, and its analgesic effects three times higher, compared with levo-ketamine, and it has fewer adverse mental effects. Borneman-Cimenti et al. (14) showed that esketamine reduces opioid consumption post-surgery, reduces the pain sensitization area, and improves rehabilitation quality. Touil et al. (15) asserted that ketamine did not prevent severe rebound pain after peripheral nerve block, and that the mechanism of rebound pain might not involve central sensitization (15). The few studies assessing rebound pain treatment with ketamine or esketamine have been contradictory or unclear. Therefore, exploring whether anti-hyperalgesia esketamine can reduce rebound pain occurrence after regional block is highly significant. This prospective, randomized controlled study is expected to fill an important gap in relevant fields and provide novel evidence for individualized pain management.

Objectives: The study described herein will be a single-center, prospective, double-blind, randomized controlled trial, with an aim to explore the effects of esketamine on postoperative rebound pain in patients undergoing TKA. Our hypothesis is that compared with the placebo group, continuous infusion of esketamine during surgery reduces the incidence of rebound pain during the first 12 h after TKA surgery.

## Method

2.

### Design and setting

2.1.

This single-center, prospective, double-blind, randomized, placebo-controlled trial will be conducted at the West Coast Hospital of the Affiliated Hospital of Qingdao University. Eligible patients will be randomly assigned to the esketamine or placebo group at a 1:1 ratio (Figure 1).

**Figure 1 fig1:**
[figure not shown]
Flow chart of participant enrollment, intervention, assessments, and visits.

### Ethics statement

2.2.

The Clinical Trial and Biomedical Ethics Committee of the Affiliated Hospital of Qingdao University has approved this trial. During the clinical trial, any protocol modifications must be filed with and approved by the Ethics Committee. Before participation, members of the research team will explain the study verbally and in writing and obtain each participant’s written informed consent. An investigator will completely and comprehensively describe the study purpose and methods, the drug’s effects, reasonably expected benefits, possible side effects, and potential risks to the participant or their designated agent. This clinical trial follows the Declaration of Helsinki, Good Clinical Practice (GCP) for Drug Clinical Trials as issued by the State Drug Administration, and other relevant regulations. It is registered in the China Clinical Trial Registration Center (ChiCTR2300069044).

### Eligibility criteria

2.3.

#### Inclusion criteria

2.3.1.

(1) Age 18–75 years; (2) body mass index (BMI) 18.5–31.9 kg/m^2^; (3) American Society of Anesthesiologists (ASA) class I–III; (4) meets TKA treatment standards including: (1) obvious knee joint pain with painless walking distance <500 meters, (2) poor effects from conservative treatment, and (3) imaging findings show apparent knee joint damage; and 4–specific disease presence including rheumatoid arthritis, osteoarthritis, traumatic arthritis, or primary or secondary osteochondral necrosis.

#### Exclusion criteria

2.3.2.

(1) hemophilic arthritis or Charcot artropothy; (2) previous ipsilateral knee joint surgical history; (3) severe cardiocerebrovascular disease (e.g., hypertension grade III, serious valvular disease, chronic heart failure, severe arrhythmia, ischemic heart disease, stroke with apparent symptoms); (4) severe liver or kidney disease (e.g., Child–Pugh score III, creatinine clearance rate < 35 ml/min); (5) nervous or mental illness; (6) past or current intracranial hypertension; (7) allergy to local anesthetics; (8) infection at the puncture site; (9) declining to participate or unable to understand written study information; (10) glaucoma; (11) hyperthyroidism with no or ineffective treatment; (12) obstructive sleep apnea (STOP-BANG score ≥ 5).

### Drop-out criteria

2.4.

Withdrawal by the investigator will occur in the events of: (1) the investigator considers it necessary to stop the trial for medical ethics reasons; (2) the participant has a severe adverse event (SAE) and their continued participation is unsuitable; (3) the investigator judges that study withdrawal is in the participant’s best interest; (4) poor study adherence by the participant.

The participant will also have the right to withdraw their consent to participate in the trial at any time, as described in their informed consent. They will also be considered to have withdrawn if they no longer accept the intervention and/or assessments or are lost to follow-up (also referred to as ‘withdrawal’ or ‘drop-out’). Reasons for drop-out will be determined to the extent possible and recorded.

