## Statistical methods

7.

We plan to include data from all the participants assigned to randomized grouping, regardless of intervention, in a intention-to-treat analysis. SPSS version 25.0 will be used to analyze data. The Shapiro–Wilk test will be used to assess normality of continuous variables. Normal data will be described as means ± standard deviations, and otherwise as medians and interquartile ranges. Demographic and intraoperative data will be compared by independent samples *t*-tests, Mann–Whitney U test, chi-square test, Yates’ chi-square test, or Fisher’s exact probability test, as appropriate. The primary study outcome (rebound pain) is dichotomous, and the relative risk (RR) and 95% confidence interval (CI) will be calculated using the modified Poisson regression model for the esketamine and placebo groups. We plan to evaluate three modified Poisson regression models: model 1 will be unadjusted; model 2 will be adjusted for gender, age, BMI, ASA grade, complications, long-term analgesics use, and baseline pain score; model 3 will be adjusted for tourniquet use time, operation time, steroid use (yes/no) and analgesic and sedative doses during the operation. We plan to conduct a sensitivity analysis on the primary outcome. The effects of the intention-to-treat set and the per-protocol set on the consistency of the primary outcome will be compared. The per-protocol set will be whether the participant has completed all main baseline variables, has not violated the inclusion or exclusion criteria, has completed all trials and assessments, and was in good adherence. Second, we plan to compare the impacts of different statistical methods (i.e., stratified chi-square test and modified Poisson regression model) on the consistency of the primary outcome. Stratified chi-square analysis adjusted for major potential confounders, i.e., age, sex, use of steroids (yes/no), preoperative pain score, and long-term use of analgesics (yes/no) before surgery. Adjusted OR values will be calculated using the Cochran–Mantel–Haenszel test (CMH).

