### Missing data handling

7.1.

The principle of intention-to-treat analysis will be used herein. Participant data may be missing due to study withdrawal, loss to follow-up, excessive side effects, or other reasons. Missing data will be processed by multiple imputations, with the imputation times set to 5 and 50 maximum iterations. A predictive mean matching model will be used for imputing continuous variables, and a logistic regression model for imputing categorical variables. After imputation, the final data will be analyzed.

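### The drop-out rules do not separate stopping the study infusion from leaving the study, which permits avoidable loss of the 12 h primary outcome and sits badly with the intention-to-treat plan

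*Protocol article*

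**What the plan says.** Three parts of the protocol article bear on this.

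- **Section 2.4, Drop-out criteria.** On the participant's side: "They will also be considered to have withdrawn if they no longer accept the intervention and/or assessments or are lost to follow-up". On the investigator's side, the grounds for withdrawal include "poor study adherence by the participant" and the case where "the participant has a severe adverse event (SAE) and their continued participation is unsuitable".
- **Section 7, Statistical methods.** "We plan to include data from all the participants assigned to randomized grouping, regardless of intervention, in a intention-to-treat analysis". Good adherence and completed assessments are conditions of the per-protocol set only.
- **Section 7.1, Missing data handling.** "Participant data may be missing due to study withdrawal, loss to follow-up, excessive side effects, or other reasons". The remedy follows: "Missing data will be processed by multiple imputations, with the imputation times set to 5 and 50 maximum iterations". Categorical variables are imputed by logistic regression.

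The sample size section (2.6) raises 160 per arm to 178 per arm for 10% withdrawal.

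**The concern.** Intention-to-treat needs the outcomes of those who deviated from treatment, as they were observed. A rule that turns treatment refusal or poor adherence into study withdrawal puts those outcomes at risk. Imputing them mainly from participants who stayed does not replace observing them.

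Here the loss would be largely avoidable. Esketamine or saline runs only from the end of spinal anaesthesia to knee closure, in an operation expected to last 1–1.5 h (sections 2.12 and 2.13's preceding dose rationale). The primary outcome covers the first 12 h after surgery (section 3.1), the diary runs to 24 h (section 2.9), and monitoring in the recovery unit and ward lasts at least 24 h (section 3.4). Ward nurses already use the participant's pain score to decide on rescue analgesia. Having stopped the drug does not prevent the outcome from being recorded.

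At stake are the completeness of the primary outcome and the value of the planned comparison of intention-to-treat with per-protocol results. If the outcomes of non-adherent participants are imputed largely from adherent ones, some of the agreement between the two sets is built in.

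**Working it through.** **1. How the rules combine.**

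- Section 2.4 joins intervention and assessments with *and/or*, so not accepting the intervention is sufficient to count as withdrawn.
- Section 7.1 lists study withdrawal among the sources of missing data and sends missing data to imputation.
- Section 2.6 treats withdrawal as lost information by enlarging the sample for it.
- Section 7 says which participants enter the analysis. It does not say that their outcomes go on being collected, and no other section does.

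That collection ends at withdrawal is therefore an inference from these sections. None of them states it.

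**2. The plan's own figures.** Inputs from section 2.6: control risk 45%, 35% lower with esketamine (read as relative), α = 0.05, power 80%. Section 7 makes tests two-sided.

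- Esketamine risk: 0.45 × (1 − 0.35) = 0.2925. Planned RR: 0.2925 / 0.45 = 0.65.
- Two-proportion formula: 147 per arm without continuity correction and 159 with it, against 160 stated. The figure reproduces within tolerance.
- Withdrawal allowance: 160 / 0.9 = 177.8, so 178 per arm and 356 in total. The allowance is 178 − 160 = 18 per arm, 36 overall.

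**3. Information at stake.** At 45% against 29.25%, without continuity correction, power is 83.4% with 160 observed per arm and 87.1% with 178. This is the most that complete follow-up could recover if the whole allowance were avoidable.

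**4. Possible bias (illustration only).** Let d be the share of the esketamine arm withdrawn and imputed at the retained participants' risk of 0.2925, and w their true risk. The documents give neither d, as a share of avoidable losses, nor w. Both are assumptions.

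True arm risk = (1 − d) × 0.2925 + d × w. True RR = that risk / 0.45. The RR reported after imputation is 0.65 in every row.

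| d | w | True esketamine risk | True RR |
|---|---|---|---|
| 10% | 29.25% | 0.2925 | 0.650 |
| 10% | 45% | 0.26325 + 0.045 = 0.30825 | 0.685 |
| 10% | 60% | 0.26325 + 0.060 = 0.32325 | 0.718 |
| 2% | 45% | 0.28665 + 0.009 = 0.29565 | 0.657 |
| 2% | 60% | 0.28665 + 0.012 = 0.29865 | 0.664 |

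**5. Losses in the placebo arm.** Suppose 10% of placebo participants are also lost, with true risk 60% but imputed at 45%.

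- True placebo risk: 0.9 × 0.45 + 0.1 × 0.60 = 0.465.
- With esketamine losses at 45%: 0.30825 / 0.465 = 0.663, close to 0.65.
- With esketamine losses no different from those retained: 0.2925 / 0.465 = 0.629. Imputation would then understate the benefit.

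The direction therefore depends on who is lost from each arm, and the documents do not settle that.

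**The case against.** The case on the other side is substantial.

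- **Nothing says that scores are discarded.** Section 7.1 imputes data that are missing; it does not make them missing. Section 7 already places non-adherent participants in the intention-to-treat set. This stands as a limit on the claim. It does not remove the problem, because including participants in a set does not ensure that their outcomes are collected, and section 2.4 classes them as withdrawn.
- **Few will refuse.** The anaesthesia team delivers a short infusion to patients who have received midazolam, so refusal once it is running must be rare. This largely stands. Table 1 places randomisation on the day before surgery, so refusal before the infusion starts is also possible, but its frequency is unknown. The adherence and adverse-event routes probably matter more.
- **Poor adherence may simply mean an unfilled diary.** The participant's main task is the diary, and where it is blank the diary outcome is missing whatever label is used. This stands in part. Withdrawing the participant still gives up later assessments that might have been obtained.
- **The full protocol or consent form may provide for continued collection.** It may. The point here is a rule that the article states, and that wording needs correcting in any case.
- **The bias figures stack assumptions.** Treating the entire 10% allowance as informative loss in one arm, with none in the other, is an extreme case. A risk of 60% exceeds the assumed placebo risk, and no reason for it is given. This stands, so the figures serve only as illustration.

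**Conclusion.** The concern holds as a defect in the stated rules. Section 2.4 does not distinguish ending the intervention from ending participation. With section 7.1, it permits avoidable missing values in an inpatient outcome and sits badly with the analysis promised in section 7.

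A reader might go further and infer that everyone who stops the infusion or adheres poorly will have an imputed outcome, and that this favours esketamine. The documents do not support either step. The end of data collection is nowhere stated. No section links side effects to more rebound pain. The dose rationale does report dose-related mental reactions, but it expects the chosen dose to avoid reactions such as dissociation, so mainly one-sided losses are an assumption.

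The size is unknown. A shift from 0.65 to 0.685 needs all of the 10% allowance to fall on esketamine participants with no recorded outcome and a true risk of 45%, with no distortion in placebo. At 2% the change is negligible, and at equal risk it is nil. The change is still worth making, because it is cheap and protects primary outcome data that can be collected.

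**What to change.** Amend sections 2.4 and 7.1:

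- Define two separate events: study infusion stopped early or not given, and consent for data collection withdrawn.
- State that all randomised participants continue the 12 h and 24 h pain assessments and the opioid and safety assessments, unless consent for data collection is withdrawn.
- Let poor adherence affect only membership of the per-protocol set, and remove it as a reason to end follow-up.
- Reserve multiple imputation for outcomes that could not be collected, and record the reason in each case.

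This concerns data collection and analysis only; it leaves clinical decisions about the infusion where they are. The cost is a change of wording and a few more ward diaries to collect.

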### Recruitment

2.5.

We plan to recruit participants for this single-center clinical trial from the Affiliated Hospital of Qingdao University through a combination of on-site and community-based methods. In clinical diagnosis and treatment, surgeons can invite the patients who they expect meet the trial conditions to participate, and anesthesiologists will use posters and leaflets in the joint surgery outpatient clinic to inform patients about the clinical trial. Qingdao University serves a large territory with a large, permanent population. The number of joint surgery clinics at the Affiliated Hospital of Qingdao University ranks among the top in the country. Therefore, a large number of potential participants are expected to meet the inclusion criteria.

